### 3.2 Sample size calculations and statistical analysis

The estimated group size was determined for the one-sided Pearson chi-square test for two proportions. We considered an alternative hypothesis of an approximately 2-fold increase in the incidence of cardiotoxicity with the presence of atherosclerotic lesions versus null hypothesis of no effect of atherosclerotic lesions. In particular, we assumed that the incidence of cardiotoxicity in the population with and without atherosclerotic lesions will vary from 60% to 75% and from 30% to 40% respectively and that the atherosclerotic lesions of various severity will be present in 30% to 40% of patients. With additional standard assumptions of 0.05 statistical significance and 80% power and assuming the estimated sample size varies from 54 to 80 individuals, thus the desired sample size of 80 was established.

Handling of missing data will depend on the proportion of cases affected by missing values. Complete case analysis will be performed if any missing values occur in less than 5% of cases. Otherwise, imputation through full conditional specification (FCS) methods are planned, accounting for the model of interest.

Statistical analysis of the results obtained in this trial will focus on the comparison of groups determined on the basis of the presence of atherosclerotic lesions, and will include a comparison of the characteristics of these groups using for comparisons of numerical variables, the Wilcoxon test, and for categorical variables the Fisher or chi-square tests. The Cochran-Armitage test on the existence of a trend for an ordinal scale variable will be used to assess the effect of the severity of atherosclerotic lesions on the incidence of cardiotoxicity.

Cumulative incidence of cancer therapy-related cardiovascular toxicity (primary endpoint) will be estimated using competing risk approach with death from other causes as the competing event. Fine and Gray’s proportional subhazards model will be used to estimate incidence by group and evaluate the impact of atherosclerotic lesions controlling for potential confounders. This model may be used in combination with missing data imputation, if necessary, with substantive model compatible fully conditional specification (SMC-FCS) imputation [24].

For time-to-event secondary endpoint (all-cause mortality) we will use the Kaplan-Meier estimates with Long-rank test to compare the survival curves. In addition, cox proportional hazard model will be used for multivariate analysis if sufficient number of events is observed. Changes in numerical variables (ejection fraction, biomarkers’ concentration) by atherosclerotic lesions status will be investigated by two-way repeated measures ANOVA.

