### 4.1 Possible limitations

As the expected frequency of cardiotoxicity according to the new 2022 guidelines is not well established there is a risk of inappropriate assumptions for power calculations, although we adopted rather conservative assumptions. In addition, as this is an observational study confounding by other cardiotoxicity risk factors is possible. If feasible, this will be accounted for in the multivariate analysis.

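### The required size of 54 to 80 follows only from particular pairings of the incidence ranges that the text does not state, so 80% power at N = 80 is not secured across the printed assumptions

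*Protocol article*

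**What the plan says.** Section 3.2 of the protocol article builds the sample size in these steps.

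- Test: "The estimated group size was determined for the one-sided Pearson chi-square test for two proportions".
- Alternative: "We considered an alternative hypothesis of an approximately 2-fold increase in the incidence of cardiotoxicity with the presence of atherosclerotic lesions".
- Incidence: "with and without atherosclerotic lesions will vary from 60% to 75% and from 30% to 40% respectively".
- Allocation: "atherosclerotic lesions of various severity will be present in 30% to 40% of patients".
- Error rates: "With additional standard assumptions of 0.05 statistical significance and 80% power".
- Result: "the estimated sample size varies from 54 to 80 individuals, thus the desired sample size of 80 was established".

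The section does not say that the two incidence ranges move together, and it does not list the scenarios that gave 54 and 80. Section 4.1 returns to the subject: "there is a risk of inappropriate assumptions for power calculations, although we adopted rather conservative assumptions".

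**The concern.** Two incidence ranges and a prevalence range are given without a pairing rule, and one range of sample sizes is presented as their consequence. A reader will take 80 as the largest size needed under those assumptions, and so will believe that 80 patients secure 80% power throughout. The remark in section 4.1 strengthens that belief.

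If the largest requirement inside the stated assumptions is above 80, the power statement is too favourable for part of the range. That affects how a null result is read. It could be taken as evidence against an effect that the study had a materially lower chance of detecting than the text implies. This calculation is the article's only justification for N = 80, and it supports the primary comparison.

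**Working it through.** **Inputs (section 3.2).** Incidence with lesions p1 = 60–75%; incidence without lesions p2 = 30–40%; lesion prevalence π = 30–40%; one-sided α = 0.05 (z = 1.645); power 80% (z = 0.842).

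**Formula.** Pooled-variance normal approximation without continuity correction, total N, with p̄ = πp1 + (1−π)p2:

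A = p̄(1−p̄) / [π(1−π)], B = p1(1−p1)/π + p2(1−p2)/(1−π)

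N = (1.645√A + 0.842√B)² / (p1−p2)²

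Power at N = 80 is Φ{[√80·(p1−p2) − 1.645√A] / √B}.

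**Step 1: reproduce the plan's figures.**

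- 60% v 30%, π = 0.30: p̄ = 0.39, A = 1.133, B = 1.100. N = (1.751 + 0.883)²/0.09 = 77.05, so 78, or 80 when rounded up to whole 3:7 blocks (24 + 56). Power at 80 is 81%.
- 70% v 35%, π = 1/3: p̄ = 0.467, A = 1.120, B = 0.971. N = (1.741 + 0.829)²/0.1225 = 53.93, so 54.
- 75% v 40%, π = 1/3: raw N = 53.17, so 54.

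Both printed ends can therefore be recovered. The value 54 needs a prevalence of about one third. At 40% prevalence, 75% v 40% needs 50.

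**Step 2: other pairs inside the printed ranges.** N and power are given for π from 30% to 40%.

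| Pair | Risk ratio | Required N | Power at N = 80 |
|---|---|---|---|
| 75 v 30 | 2.50 | 34 to 30 | 99% or more |
| 75 v 37.5 | 2.00 | 49 to 43 | 94–97% |
| 75 v 40 | 1.88 | 57 to 50 | 91–94% |
| 60 v 30 | 2.00 | 78 to 69 | 81–85% |
| 65 v 35 | 1.86 | 79 to 70 | 81–85% |
| 70 v 40 | 1.75 | 79 to 69 | 81–85% |
| 60 v 32 | 1.88 | 90 to 80 | 76–80% |
| 60 v 33 | 1.82 | 97 to 86 | 73–78% |
| 60 v 35 | 1.71 | 114 to 101 | 67–72% |
| 65 v 40 | 1.63 | 115 to 101 | 66–71% |
| 60 v 40 | 1.50 | 181 to 159 | 50–54% |

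With every pair allowed, N runs from 30 to 181.

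**Step 3: restrict to a roughly two-fold effect.** Take risk ratios of 1.8–2.2 as the reading of the alternative; this interval is an assumption of the check. N then runs from about 37 (75% v 34.25%, ratio 2.19, at 40% prevalence) to about 97 (60% v 33% at 30% prevalence). At the exact 1.8 limit, 60% v 33.3%, it reaches 100.

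Worked example, 60% v 32% at π = 0.30: p̄ = 0.404, A = 1.147, B = 1.111. N = (1.761 + 0.887)²/0.0784 = 89.5, so 90. Power at 80 = Φ[(2.504 − 1.761)/1.054] = Φ(0.705) = 76%. Its ratio is 60/32 = 1.875, identical to 75/40 = 1.875, one of the pairs that yields 54.

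**Step 4: where 80 stops being enough.** With 60% in the lesion group and 30% prevalence, N stays at or below 80 only while the rate without lesions is at most about 30.5%.

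**The case against.** The strongest defence is that the sentence fixing a roughly two-fold increase governs the ranges, which merely illustrate it: a baseline of 30–40%, about doubled, gives 60–75%. On that reading low goes with low and high with high, and 80 and 54 are recovered. The printed minimum also supports pairing, because free combination would give about 30 rather than 54. This much stands. A reader might infer that the sample size contains an arithmetic error; the documents do not support that.

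A reader might also infer from the table that the study has only about 50% power under its own alternative. That does not hold either. The figure belongs to 60% v 40%, a 1.5-fold increase and so outside the stated alternative. It is a corner of the printed ranges, not the design scenario.

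It is fair to add that section 4.1 openly admits the assumptions may be wrong, and that a condensed article may leave a scenario list to the full protocol.

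The defence still leaves a gap. The pairing is the reader's inference. If 1.875-fold counts as roughly double at 75% v 40%, it must also count at 60% v 32%, where 80 patients fall short at 30% prevalence. The issue is also more than an omitted list: the article prints a range of sizes that its printed inputs do not yield, and then describes those inputs as conservative.

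**Conclusion.** The point holds as a misstatement of what 80 patients secure, not as a calculation error and not as proof that 80 is the wrong number. The range 54 to 80 corresponds to selected pairs about 30–35 points apart. The printed ranges give about 30 to 181, and ratios of 1.8–2.2 within them give about 37 to 97. Within that roughly two-fold band, power at N = 80 falls to about 73% at 60% v 33%. For weaker contrasts still inside the printed ranges it is 66–72% (60% v 35%, 65% v 40%).

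The clause "although we adopted rather conservative assumptions" is not supported. At 60% v 30% with 30% prevalence, 80 patients give 81% power, which leaves almost no margin.

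These figures rest on the one-sided 5% test and prevalence range that the article states, on the normal approximation, and on all 80 patients contributing an outcome. Exact enumeration of the one-sided Pearson test changes little: 82.5% at 60% v 30% with 30% prevalence, and 51–55% at 60% v 40%.

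**What to change.** Keep N = 80 and change the wording in two places.

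- **Section 3.2:** state the pairs of incidence and the prevalence that gave 54 and 80. Replace the general claim with one the numbers support: within the printed incidence ranges, 80 patients give at least 80% power (one-sided 5%) for an absolute difference of about 30 percentage points or more, with lesion prevalence of at least 30%. Add a short table of power at N = 80 for smaller contrasts: 60% v 35% (67–72%), 65% v 40% (66–71%), and 60% v 40% (50–54%), the last marked as 1.5-fold and outside the two-fold alternative.
- **Section 4.1:** delete the clause "although we adopted rather conservative assumptions" and keep the admission of uncertainty that precedes it.

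No endpoint, analysis or recruitment target changes. The cost is that the stated power becomes less favourable in part of the range.

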### 1.1 Study aims

Assessment of the prognostic value of the coronary atherosclerosis and the CAC score before chemotherapy for the occurrence of the cardiovascular toxicityEvaluation of IL-6, MPO and TNF-alpha for use in the diagnosis of cardiotoxicity during oncological treatment.Influence of studied parameters, i.e. presence of atherosclerosis, echocardiographic parameters and biomarker levels on the prognosis of patients undergoing cardiotoxic chemotherapy

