### 2.2 Study patients

The study will include patients with cancer, diagnosed and qualified for further systemic treatment with high-dose anthracycline chemotherapy at the Maria Sklodowska-Curie National Research Institute of Oncology in Warsaw. Patients must give informed and voluntary consent to participate in the study and meet all the inclusion criteria and none of the exclusion criteria listed in Table 1.

**Table 1 pone.0288146.t001:** Inclusion and exclusion criteria.

Inclusion criteria
1. Eastern Cooperative Oncology Group (ECOG) performance status from 0 to 2.
2. Age ≥18 years at the time of signing the informed consent.
3. Known neoplastic disease prior to the initiation of chemotherapy with a high dose of anthracyclines (doxorubicin ≥ 240 mg / m2 b.w. or epirubicin ≥ 600 mg / m2 b.w.)
4. No history of heart failure (left ventricular ejection fraction ≥ 50% as assessed by echocardiography).
5. No history of: coronary artery disease, stroke and lower limb atherosclerosis
6. At least moderate baseline cardiovascular toxicity risk according to Heart Failure Association–International Cardio-Oncology Society stratification [1]
Exclusion criteria
1. History of heart failure and/or left ventricle ejection fraction <50%
2. Significant valvular heart disease
3. Previous chemotherapy or radiation to the chest
4. Presence of any disease with a life expectancy <1 year in the opinion of the investigator.
5. Drug or alcohol abuse
6. Lack of possibility or contraindications for computed tomography (CT) scan.

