### 2.3 Study visits and follow up

Approximately 80 patients are planned to be included in the study. Each patient will have 5 program visits every 3 months for 12 months. At the first visit, the patient will be informed about the type of the proposed follow-up, its course and planned tests. After signing the consent to participate in the study, patients will undergo planned procedures according to the schedule shown in Table 2.

**Table 2 pone.0288146.t002:** Schedule of Activities (SoA).

Visit	1	2	3	4	5
Days from first Visit window	1	90 (±14)	180 (±14)	270 (±14)	360 (±14)
Informed Consent	x				
In-/exclusion criteria	X				
Medical History/ Concomitant diagnoses	x				
Demographics	x				
NYHA classification	X	X	X	X	X
ECOG performance status	X	X	X	X	X
Physical exam	X	X	X	X	X
Concomitant Therapy	X	X	X	X	X
Assessment of Endpoints		X	X	X	X
12-lead-ECG	X	X	x	X	x
Echocardiography with GLS assessment	x	X	X	X	X
Lab test	x	X	X	X	X
CCTA	x				
IL-6, MPO, TNF-alpha	x		x		x

**Abbreviations**: ECG = electrocardiogram; ECOG = Eastern Cooperative Oncology Group; GLS = global longitudinal strain; NYHA = New York Heart Association; CCTA = Coronary Computed Tomographic Angiography

Clinical variables such as: age, gender, cardiovascular risk factors (hypertension, diabetes, hyperlipidemia, obesity, smoking status), alcohol use, previous medical history, concomitant heart failure therapy, statins or other lipid lowering medications will be documented at baseline and then checked at each visit. Lipid levels and diabetes status at each visit will be determined using a fasting blood sample and lipid panel at that visit.

Cancer diagnosis and current treatment (including cumulative dose of anthracyclines) will be collected and documented at each visit.

In all patients, a single coronary computed tomographic angiography (CCTA) will be performed at the beginning of the study, with calculation of coronary artery calcium (CAC) score according to the Agatston method. Contrast cardiac CT scanning for CAC quantification will be performed with a 64-slice CT scanner (Revolution Evo, GE Healthcare, Waukesha, USA) with prospective ECG triggering. A tube voltage of 120kVp will be used. Images will be reconstructed with a slice thickness of 0.625 mm and CACS was quantified using the Agatston method with dedicated software by a well-trained researcher.

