#### 2.4.2 Secondary endpoints

The secondary composite endpoint include: time to all-cause death, cardiovascular death, myocardial infarction, and stroke.

Other secondary endpoints include: (1) the severity of atherosclerosis in the coronary arteries and the calcification index in computed tomography, (2) the percentage decrease in left ventricular ejection fraction and GLS in echocardiography, (3) changes in the concentration of biomarkers involved in inflammatory and atherosclerotic processes.

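### The yes/no lesion comparison is adjusted, but lesion severity gets only an unadjusted trend test and the CAC score is related to cardiotoxicity in no stated analysis

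*Protocol article*

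**What the plan says.** Section 1.1 gives as the first aim "Assessment of the prognostic value of the coronary atherosclerosis and the CAC score before chemotherapy for the occurrence of the cardiovascular" toxicity, so two CT predictors are named. Section 2.3 provides one baseline CT scan for all patients, "with calculation of coronary artery calcium (CAC) score according to the Agatston method". Section 2.4.2 lists "the severity of atherosclerosis in the coronary arteries and the calcification index in computed tomography" among the secondary endpoints.

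Section 3.2 states that the analysis "will focus on the comparison of groups determined on the basis of the presence of atherosclerotic lesions". For the primary endpoint it plans a competing-risk analysis with death from other causes as the competing event, and a Fine-Gray model that estimates incidence by group and assesses lesions with adjustment for potential confounders. Severity is handled separately: "The Cochran-Armitage test on the existence of a trend for an ordinal scale variable will be used to assess the effect of the severity" of lesions on cardiotoxicity incidence. The rest of the section covers mortality (Kaplan-Meier, log-rank, Cox) and changes in ejection fraction and biomarkers by lesion status (repeated-measures ANOVA). The CAC score is not mentioned in any of these analyses.

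On confounding, section 1 says that the risk factors for cardiotoxicity coincide with those for atherosclerosis. Section 4.1 concedes that confounding is possible and adds: "If feasible, this will be accounted for in the multivariate analysis". Table 1 in section 2.2 requires "At least moderate baseline cardiovascular toxicity risk according to Heart Failure Association"–International Cardio-Oncology Society (HFA-ICOS) stratification, so that category is known for every patient at entry.

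**The concern.** The aim and the analysis do not line up. Of the CT measures that the aim covers, only the coarsest, any lesion or none, enters a model that adjusts for confounders and handles competing death. Severity goes to a test that does neither, and CAC goes to no outcome analysis.

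If patients with more extensive lesions also have more hypertension, diabetes or higher age, a positive severity trend has two explanations that the stated test cannot tell apart: lesions matter in their own right, or they mark shared risk factors. And if the study reports on CAC, the analysis will not have been fixed in this document. Section 4 offers the study as a way to identify further patient groups for preventive statin treatment, and that use depends on the graded information.

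**Working it through.** **1. Predictors set against analyses (sections 1.1, 2.3 and 3.2)**

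| CT measure | Stated analysis against cardiotoxicity | Covariates | Timing and competing death |
|---|---|---|---|
| Lesions present or absent | Fine-Gray model | potential confounders | handled |
| Lesion severity | Cochran-Armitage trend test | none | not handled |
| CAC score | none stated | – | – |

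The Wilcoxon comparison of group characteristics could describe CAC in patients with and without lesions. That relates CAC to lesions, not to cardiotoxicity.

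**2. The plan's sample size.** Inputs from section 3.2: one-sided chi-square test, alpha 0.05, power 80%, incidence 60% with and 30% without lesions, lesions in 30% of patients. With k = 0.70/0.30 = 7/3 and pooled rate 0.3×0.60 + 0.7×0.30 = 0.39:

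n(lesions) = [1.645·√(0.39×0.61×(1+3/7)) + 0.842·√(0.60×0.40 + 0.30×0.70×3/7)]² / 0.30² = [0.959 + 0.483]² / 0.09 ≈ 23.1, rounded up to 24.

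n(no lesions) = 24×7/3 = 56. The total is 80, as stated, with power 81.3%. The calculation covers the yes/no split only; none is given for severity or CAC.

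**3. Events available for adjusted models** (80 patients, rates from section 3.2)

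- Low end: 80×(0.3×0.60 + 0.7×0.30) = 80×0.39 = 31.2.
- High end: 80×(0.4×0.75 + 0.6×0.40) = 80×0.54 = 43.2.

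At 10 events per term (an assumption, not in the article) this allows 3.1 to 4.3, or about 3 to 4 terms. One severity term plus one or two degrees of freedom for risk category uses 2 to 3 terms. CAC in two parts (zero or not, plus log score) with the same adjustment uses 3 to 4, and 4 fits only towards the high end.

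**4. Illustration of the bias in the trend test.** The article gives no figures for this, so every input is assumed: 80 patients; four severity levels with 35% having lesions (mid-range of the stated 30% to 40%); event rate about 45%; severity with no effect; one confounder correlated 0.2 to 0.6 with underlying severity and with an odds ratio of 1.5 to 2.5 per SD for toxicity. There were 3,000 runs per setting for the trend test and 1,000 for the adjusted model.

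| Correlation, OR per SD | Trend test, one-sided 5% | Trend test, two-sided 5% | Logistic model with the confounder, one-sided 5% |
|---|---|---|---|
| 0.2, 1.5 | 8.8% | 6.2% | 5.3% |
| 0.4, 2.0 | 22.8% | 15.1% | 4.7% |
| 0.6, 2.5 | 52.7% | 40.5% | 4.6% |

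Over all nine settings the adjusted model rejected in 4.4% to 6.1%. It adjusts for the exact confounder, so real data would keep some residual confounding. The simulation has no censoring or competing deaths and does not measure the cost of ignoring them.

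**The case against.** The strongest reply is that the primary analysis is already adjusted and handles competing death. This is correct. A reader might infer that the whole prognostic question rests on confounded comparisons, and the text does not support that. Nor does the section 4.1 remark about feasibility undo the adjustment: it stands under limitations, while the statement in section 3.2 is unconditional.

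Four other stronger readings also fail.

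- **A crude risk ratio inflated by 13% to 23%.** With a risk factor in 60% of patients with lesions and 30% of those without, and a risk ratio of 1.5 to 2 (all assumed), the bias factor is 1.30/1.15 = 1.13 to 1.60/1.30 = 1.23. This is the crude yes/no contrast, which the plan adjusts, so it does not size the severity problem.
- **The severity gradient is discarded.** It is not; the trend test uses it, though without adjustment.
- **A positive trend would merely show that sicker patients have more plaque.** The test relates severity to cardiotoxicity. Confounding is one possible explanation of a positive result, not what the test demonstrates.
- **HFA-ICOS risk is left out.** Section 3.2 does not list its confounders, and an unlisted set does not show that a variable is excluded.

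It can also be said that prognostic value may mean a plain association, for which an unadjusted trend is valid, and the simulated rejections do reflect a marginal association that is present in the data. But section 3.2 speaks of the effect of severity and adjusts the yes/no comparison, so the article itself is after more than a marginal association.

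Finally, the coding of CAC is ordinary material for an analysis plan that is not shown, and the undefined ordinal scale could be CAC-based. This softens the CAC half. It does not remove it, because the section assigns methods to the other main measures, and a CAC-based scale would still get only the unadjusted test. The words on atherosclerotic lesions in the Fine-Gray sentence could be stretched to include severity, but the model works by group and groups are defined by presence.

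**Conclusion.** The point holds for severity and CAC, and not for the presence/absence comparison. Severity is assigned to a method that cannot deal with the confounding the article itself describes or with the competing event it defines. CAC, named in the first aim, has no stated analysis against cardiotoxicity.

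The size of the bias cannot be fixed from the article. Under the assumed range, a one-sided 5% trend test rejects in 9% to 53% of trials when severity has no independent effect; the span shows that the result depends on the assumptions. The practical effect of ignoring competing death is also unknown and may be small, given 12 months of follow-up and the exclusion of patients with life expectancy under one year. That adjusted models are feasible rests on the article's own rates (31 to 43 events) and on the assumed 10 events per term.

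**What to change.** In section 3.2, add two further Fine-Gray models for the primary endpoint:

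1. Lesion severity as an ordinal score, with the scale defined.
2. The CAC score, for example log(CAC+1), or zero/non-zero plus the log score if many patients score zero.

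Adjust each for a short pre-named set, such as baseline HFA-ICOS risk category, and keep the total to about 3 to 4 terms. Keep the Cochran-Armitage test as a descriptive summary. Any change in C-index would be imprecise with 31 to 43 events and should be labelled exploratory. Aligning the section 4.1 remark on feasibility with section 3.2 is optional.

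The cost is wording, one or two degrees of freedom for the risk category, and some extra analysis. The scan and the risk category are already collected for every patient, so no new patients, visits or measurements are needed.

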## 2. Methods

### 2.1 Study structure

The ANTEC Trial is a single-center, prospective, observational trial evaluating the impact of atherosclerosis in the coronary arteries determined by computed tomography on the risk of cardiotoxicity related to anthracycline-based chemotherapy. The trial is being carried out in accordance with the principles of the Declaration of Helsinki and the International Conference on Harmonization Good Clinical Practice guidelines. The conduct of the study is approved by an Independent Ethics Committee at the Maria Sklodowska-Curie National Research Institute of Oncology in Warsaw (the date of approval– 28 October 2021, approval no. 80/2021) and all participants will provide written informed consent before study entry. The registration identifier on clinicaltrials.gov is NCT05118178.

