## 5. Conclusion

This is the first study to prospectively evaluate the influence of asymptomatic atherosclerosis in coronary arteries on chemotherapy-related cardiac dysfunction. This work may contribute to a better understanding of the pathophysiology of cardiotoxicity and to changing the standards of management and improving survival in oncological patients.

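### One Fine-Gray model is asked both for incidence by group and for the adjusted impact of lesions; its ratio alone cannot be read as an effect on cardiotoxicity, although the likely distortion is small

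*Protocol article*

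**What the plan says.** Section 3.2 says that the cumulative incidence of the primary endpoint "will be estimated using competing risk approach with death from other causes as the competing event". It then names a single regression, the Fine-Gray model, which "will be used to estimate incidence by group and evaluate the impact of atherosclerotic lesions", with adjustment for confounders. That one sentence covers two tasks: describing how many patients in each group develop cardiotoxicity, and measuring what lesions do to cardiotoxicity once confounders are held constant.

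The purpose of the study is worded in both ways. The first aim in section 1.1 is prognostic value. Section 2.1 describes a study "evaluating the impact of atherosclerosis in the coronary arteries determined by computed tomography on the risk of cardiotoxicity", and section 5 hopes for a "better understanding of the pathophysiology of cardiotoxicity".

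The article names no cause-specific model for cardiotoxicity. The other planned comparisons of cardiotoxicity in section 3.2 (chi-square or Fisher, Cochran-Armitage) also compare incidence. All-cause mortality is analysed separately, by Kaplan-Meier and log-rank, with a Cox model if there are enough events.

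**The concern.** In a Fine-Gray model a patient who dies without cardiotoxicity stays in the risk set. The subdistribution ratio therefore depends on two rates: cardiotoxicity among patients still alive, and death. If patients with lesions die more often at the same covariate values, the ratio falls even when their rate of cardiotoxicity while alive is unchanged.

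That is a proper feature when the question is how many patients will develop cardiotoxicity. It is a drawback when the adjusted ratio is offered as the impact of lesions on the heart, or as evidence on mechanism. A ratio somewhat below the cause-specific one could then reflect more deaths rather than a weaker link with cardiotoxicity, and no other planned analysis gives the cause-specific ratio for cardiotoxicity that would separate the two.

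**Working it through.** **Inputs from section 3.2.** Cardiotoxicity: "the incidence of cardiotoxicity in the population with and without atherosclerotic lesions will vary from 60% to 75% and from 30% to 40% respectively". Lesion prevalence: "the atherosclerotic lesions of various severity will be present in 30% to 40% of patients". N = 80, one-sided alpha 0.05, power 80%.

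**The plan's own figure.** For 60% v 30% at 30% prevalence, k = 3/7 and the pooled proportion is 0.3×0.6 + 0.7×0.3 = 0.39. With the pooled one-sided formula:

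n0 = [1.645√(0.39×0.61×(1+7/3)) + 0.842√(0.3×0.7 + 0.6×0.4×7/3)]² / 0.30² = 53.9

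N = 53.9 × (1 + 3/7) = 77.05, which is 80 when rounded up to a whole 3:7 split. This reproduces the upper end of the stated range, so 60% v 30% is used as the planning scenario below.

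**Inputs assumed.** The document gives no death rates. Deaths are entered as the 12-month probability of death that would apply without cardiotoxicity. Hazards are taken as constant, and no covariates are used.

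**Cause-specific ratio.** Cumulative hazards of cardiotoxicity are −ln(0.70) = 0.357 without lesions and −ln(0.40) = 0.916 with lesions. The ratio is 0.916/0.357 = 2.57.

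**Implied subdistribution ratio.** With cumulative hazards lt (cardiotoxicity) and ld (death), cumulative incidence is F = lt/(lt+ld) × (1 − exp(−(lt+ld))), and the ratio is ln(1−F1)/ln(1−F0).

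Worked line, deaths 10% v 5%: ld = 0.105 and 0.051; F1 = 0.574 and F0 = 0.293; ratio = 0.853/0.347 = 2.46. For the null, lt = 0.357 in both groups: F1 = 0.286, ratio = 0.336/0.347 = 0.97.

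| Assumed deaths, lesions v none | True ratio 2.57 appears as | True ratio 1.00 appears as |
|---|---|---|
| 5% v 5% | 2.55 | 1.00 |
| 10% v 5% | 2.46 | 0.97 |
| 15% v 5% | 2.37 | 0.94 |
| 25% v 10% | 2.26 | 0.91 |
| 30% v 10% | 2.17 | 0.88 |

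**Cross-check.** Solving the large-sample Fine-Gray score equation at 35% prevalence, without censoring, gives 2.48 at 10% v 5% and about 2.4 at 15% v 5%. Direction and size agree.

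**Effect of adjustment.** Assume that age alone drives death (25% in older, 5% in younger patients), that lesions have no effect on death at a given age, and that 70% of lesion patients and 25% of the others are older. Crude deaths are 0.7×25% + 0.3×5% = 19% and 0.25×25% + 0.75×5% = 10%. In simulation at a cause-specific ratio of 2.57, the Fine-Gray ratio is about 2.38 unadjusted and 2.50 adjusted for age. Most of the shift goes.

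**Shift against precision.** Expected events at 30% prevalence: 80 × (0.3×0.6 + 0.7×0.3) = 31.2. The approximate standard error of the log ratio is 1/√(31.2×0.3×0.7) = 0.39, so the 95% interval is a factor of exp(1.96×0.39) = 2.15 each way. At 40% prevalence there are 33.6 events and the factor is 1.99. The shift from 2.57 to 2.46 is 0.11 to 0.12 standard errors; to 2.37 it is 0.20 to 0.23.

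**The case against.** The strongest reply is that Fine-Gray targets the quantity the protocol asks for. The first aim is prognostic, and section 3.2 frames the alternative hypothesis as "an approximately 2-fold increase in the incidence of cardiotoxicity with the presence of atherosclerotic lesions". In section 2.1, impact is on risk, which can be read as incidence. On that target 2.46 is not an understated 2.57; it is the correct value of a different quantity. The sentence in section 5 is a closing hope rather than an objective. All of this stands, and it is why Fine-Gray should stay.

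The reply on size also largely stands. Follow-up is 12 months, patients with a life expectancy under one year are excluded, and those with known coronary disease, stroke or lower limb atherosclerosis are not eligible. Nothing in the document supports the last two rows of the table. The model is adjusted, and adjustment removes most of the shift when shared risk factors drive the deaths. One reservation: section 4.1 promises multivariable adjustment only where feasible, and about 31 to 34 events allow few covariates.

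The planned mortality analysis will show whether death differs by lesion status, so a reader will have a warning when the issue applies. It does not give a cause-specific ratio for cardiotoxicity.

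Finally, companion models often sit in an analysis plan that is not shown, and their absence from an article is not in itself a fault. The point here is narrower: the article does assign the adjusted impact question to the Fine-Gray model.

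**Conclusion.** The point holds as a modest matter of interpretation and reporting. The Fine-Gray ratio answers the incidence and prognostic questions; by itself it does not answer whether lesions act on cardiotoxicity. Under assumed, unadjusted deaths of 10% v 5% to 15% v 5%, the ratio would be about 4% to 8% below the cause-specific one (2.46 to 2.37 against 2.57). The shift is smaller after adjustment for shared risk factors, and negligible if deaths are equal. These figures rest on constant hazards and on death rates that the document does not give.

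A reader might infer that Fine-Gray is the wrong model here, that a real effect will be materially understated, or that lesions could come out as protective. The documents do not support any of these. The model matches the first aim and the stated hypothesis. A material understatement would need lesions to raise 12-month death well beyond what the covariates explain, which nothing in the text suggests. A null appearing as 0.97 or 0.94 could not be told from 1 with intervals this wide.

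**What to change.** In section 3.2, keep the cumulative incidence curves and the Fine-Gray model for incidence by group and for the prognostic aim. Add two cause-specific Cox models with the same covariates, one for cardiotoxicity (deaths without cardiotoxicity censored) and one for death without prior cardiotoxicity. Report their ratios beside the Fine-Gray ratio, and state that conclusions about impact or mechanism rest on the cause-specific ratio for cardiotoxicity.

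The cost is one more set of models on data already being collected and a sentence or two of text; the sample size does not change. The downsides are that several ratios must be explained and that the death model will be imprecise if deaths are few. The cause-specific ratio is no cure for confounding and is only as good as the adjustment that the number of events allows.
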